The determination of the specific angle for each exercise and participant will be individualised. This will be monitored by the qualified personal trainer or principal investigator, guided by the following principles to ensure effectiveness, safety and comfort:Assessment of Active and Comfortable Range of Motion (ROM): The participant’s active and pain-free ROM for the main joint will be assessed at the beginning of the exercise, avoiding extreme ranges that generate discomfort, pain or instability, considering their ‘specific motor restrictions’.Selection of the Intermediate Angle within the Safe Range: An intermediate angle within the comfortable ROM will be selected that seeks to avoid joint locking or excessive passive tension, and allows the participant to generate a stable and effective Maximal Voluntary Isometric Contraction (MVIC). Although the peak torque angle will not be exhaustively sought, the practitioner will guide the participant to a position in the middle zone of their safe ROM where they subjectively report that they feel comfortable exerting force, favouring optimal actin and myosin overlap.Prioritisation of Safety and Tolerability: If in doubt, the angle that warrants the greatest perceived safety and comfort will be prioritised, even if it is not the theoretically ’optimal’ angle for maximal force production.Recording and Consistency: The individualised intermediate angle, once determined and accurately measured (HALO© digital goniometer), will be recorded and used consistently across all training sessions and MVIC assessments, ensuring standardised stimulus presentation. The aim of this process is to select a joint angle that represents a significant muscular challenge and allows for high fibre activation, within a zone that is biomechanically safe, personalised and well tolerated by each older adult.

The exercises to be performed are: peck deck, pull over, lateral shoulder raise, leg extension, leg curl, lumbar, hip abduction and hip adduction. A visual demonstration of these exercises is shown in Figure 1. The detailed standards for their application (positioning, main muscles, individualised determination of angles, instructions for the three contraction phases and monitoring points) are presented in Table 3.

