#### 2.1.3. Control Mechanisms for Field Protocol Standardisation

To ensure a standardised and rigorous implementation of the protocol and the quality of the data, the following control mechanisms will be put in place:Training of Research Staff: All staff directly involved in the intervention and evaluation (principal investigator, evaluation professionals, qualified personal trainer) will receive specific and detailed training on all study procedures. The ‘qualified personal trainer’ should have a degree in Physical Activity and Sports Science or Physiotherapy, with demonstrable experience in working with older adults and strength training. Training will cover: consistent application of inclusion/exclusion criteria; accurate technique for individualised determination of joint angles (HALO© digital goniometer); correct instruction, supervision and progression of IST exercises (CIEX System machine, Chronojump software with feedback); standardised administration of questionnaires; and accurate performance of all assessment tests. Recalibration sessions or periodic team meetings may be held to ensure consistency.Standardisation of the Intervention (IST Programme): The application of the IST will strictly follow the set progressive 16-week design (single set per muscle group, gradual increase of total stimulus duration and intensity of submaximal phases), as detailed in Table 2. The correct technical performance of the 8 specific exercises will be guided by the standards provided in Figure 1 and Table 3. The use of the CIEX SYSTEM machine with real-time feedback is essential in ensuring that target intensities are met. All sessions will be held individually and will be directly supervised by qualified personnel.Standardisation of Assessment Procedures and Minimisation of Bias: To minimise potential bias during assessments, standardised protocols for each test and data collection (detailed in Section 2.2) will be strictly followed, including specific recommendations (e.g., EWGSOP, InBody manufacturer). All assessment personnel shall be trained. Calibrated instruments and objective measures (CIEX System, InBody 230, Newtest Powertimer) shall be used. As far as possible, assessors will not have access to the previous results of participants to avoid expectation bias. If the analysis of the static posture photographs is conducted by a different individual, an effort will be made to blind them to the time point (pre/post) during the assessment. Although complete blinding of primary assessors at the time point is difficult in this design, strict adherence to protocols and the use of objective measures are the primary strategies to reduce observer bias.Monitoring of Adherence, Compliance and Concomitant Variables: Attendance to training sessions and assessments will be recorded in detail, and adherence to protocol criteria will be continuously monitored (e.g., ≥90% sessions, assessments on time). Changes in usual medication (by asking at assessments and training visits) will be recorded by referring to the baseline information in Section 2.1.1. Participants will be instructed to maintain their usual dietary and physical activity habits, not initiating new diets or intense exercise programmes; compliance will be monitored informally, and significant changes will be recorded. Standardised Case Report Forms (CRFs) will be used and made available for ethical consultation or audit if required.Strategies to Promote Retention and Completion of Follow-up: Individualised and flexible scheduling, close supervision with motivational support, regular communication, and the possibility of extending the intervention period to make up for excused absences will be used to promote retention. The importance of completing all phases will be explained. If a participant discontinues the IST, they will be encouraged to complete the post-intervention assessment (week 17) if feasible, to collect outcome data from as many participants as possible (providing intention-to-treat analysis). Data collected until withdrawal will be retained and managed according to the Section 2.3 (‘Statistical Analysis’).

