1.Other Indicators of Sarcopenia and Dynapenia:○Handgrip Strength: Specific measurement variable: Maximal handgrip strength, measured in kilograms (kg) (Jamar Dynamometer). Analysis metric: Absolute change from baseline to week 17. Method of aggregation: Mean and SD. Time point(s): Baseline (week 0) and post-intervention (week 17). Clinical Relevance: A component of the sarcopenia diagnosis and a predictor of functionality and mortality.○Gait Speed: Specific measurement variable: Usual gait speed over a 4 m course, measured in meters/second (m/s) (Newtest Powertimer). Analysis metric: Absolute change from baseline to week 17. Method of aggregation: Mean and SD. Time point(s): Baseline (week 0) and post-intervention (week 17). Clinical Relevance: A measure of physical performance, a component of the sarcopenia diagnosis, and a predictor of adverse outcomes.○MVIC of other muscle groups: Specific measurement variable: MVIC for the peck deck, pull over, lateral shoulder elevation, leg curl, low back, hip abduction and hip adduction, measured in Newtons (N) (CIEX SYSTEM). Analysis metric: Absolute change from baseline to week 17. Method of aggregation: Mean and SD of the change per exercise. Time point(s): Baseline (week 0) and post-intervention (week 17). Clinical Relevance: Assesses the training response across different body regions.○Sarcopenia Status: Specific measurement variable: Diagnostic status of sarcopenia according to EWGSOP2 criteria (based on muscle strength, muscle mass, and physical performance). Analysis metric: Change in the proportion of participants meeting the diagnostic criteria from baseline to week 17. Method of aggregation: Frequencies and percentages. Time point(s): Baseline (week 0) and post-intervention (week 17). Clinical Relevance: Quantifies the overall impact of the intervention on the diagnostic status of the condition.2.Health-Related Quality of Life (HRQoL):○Specific measurement variable: The index score derived from the EQ-5D-5L descriptive system and the Visual Analogue Scale (VAS) score of the same questionnaire. Analysis metric: absolute change from baseline to week 17 for both the index score and the VAS score. Method of aggregation: Mean and SD of the changes. Time point(s): Baseline (week 0) and post-intervention (week 17). Clinical Relevance: Measures the overall self-perceived health and the impact of the intervention on multiple dimensions of participant well-being.3.Applicability of the IST Protocol:○Perceived Safety: Specific measurement variable: Score on a 5-point Likert scale for perceived safety. Analysis metric: Mean score post-intervention. Method of aggregation: Mean and SD. Time point(s): Post-intervention (week 17). Relevance: Assesses the participant’s subjective perception of safety, providing data to test hypothesis H1.○Acceptance/Satisfaction: Specific measurement variable: (1) Adherence rate (% of completed sessions); (2) Score on a 5-point Likert scale for overall satisfaction. Analysis metric: Percentage for adherence; Mean score post-intervention for satisfaction. Method of aggregation: Percentage for adherence; Mean and SD for satisfaction score. Time point(s): Adherence monitored continuously during the intervention (weeks 1–16); Satisfaction assessed post-intervention (week 17). Relevance: Measures the feasibility and appeal of the intervention to participants, providing data to test hypothesis H2.○Perceived Difficulty: Specific measurement variable: Score on a 5-point Likert scale for perceived difficulty. Analysis metric: Mean score post-intervention. Method of aggregation: Mean and SD. Time point(s): Post-intervention (week 17). Relevance: Evaluates the perception of technical simplicity, providing data to test hypothesis H3.○Adverse events: Specific measurement variable: Incidence, type, severity and causality (relationship to IST). Analysis metric: Frequencies and descriptive summary. Method of aggregation: Counts and percentages. Time point(s): Monitored continuously during the intervention period (weeks 1–16). Relevance: Assesses the objective safety profile of the protocol, providing data to test hypothesis H1.

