Leg Extension	d	Quadriceps	Sitting on the CIEX machine with back against the backrest, hips flexed 90°, and knees flexed 90°.	*	Push the supports forward without movement, hold the contraction for the specified time in the three phases of progressive intensity while breathing continuously.	Avoid hip extension, avoid lumbar spine extension, do not perform the Valsalva manoeuvre, and ensure there is no visible joint movement.
Leg Curl	e	Hamstrings	Sitting on the CIEX machine with back against the backrest, hips flexed 90°, and knees flexed 90°.	*	Push the supports back without movement, hold the contraction for the specified time in the three phases of progressive intensity while breathing continuously.	Avoid hip flexion, avoid trunk flexion, do not perform the Valsalva manoeuvre, and ensure there is no visible joint movement.
Low Back	f	Square lumbar	Sitting on the CIEX machine with 60° hip flexion and shoulder blades resting on the support.	*	Push the support backwards, extending the lumbar spine without movement, hold the contraction for the specified time in the three phases of progressive intensity while breathing continuously.	Avoid trunk offsets, do not perform prolonged Valsalva manoeuvres, and ensure that there is no visible joint movement.
Hip Abduction	g	Gluteus maximus, gluteus medius and gluteus minimus.	Sitting on the CIEX machine with back against the backrest, with 45° hip extension, full knee extension and the inside of the feet resting on the supports.	*	Push the supports inwards without movement, hold the contraction for the specified time in the three phases of progressive intensity while breathing continuously.	Avoid hip and trunk extension, do not perform the Valsalva manoeuvre, and ensure there is no visible joint movement.
Hip Adduction	h	Adductor magnus, adductor magnus, adductor longus, pectineus and gracilis.	Sitting on the CIEX machine with back against the backrest, with 45° hip extension, 100° knee flexion and the outside of the knees resting on the supports.	*	Push the supports out without movement, hold the contraction for the specified time in the three phases of progressive intensity while breathing continuously.	Avoid hip and trunk flexion, do not perform prolonged Valsalva manoeuvre, ensure that there is no visible joint movement.

* Intermediate, determined individually according to the principles described in Section 2.1.2 (under ‘Determination of the specific angle’).

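### Table 3 describes hip abduction as an inward push and hip adduction as an outward push, so two of the seven secondary MVIC outcomes could be reported under the opposite muscle group

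*Protocol article*

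**What the plan says.** Table 3 (Application Standards for IST Programme Exercises) gives each exercise a name, main muscles, a position and a push instruction.

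- **Hip Abduction.** Muscles: "Gluteus maximus, gluteus medius and gluteus minimus". Position: seated, with "full knee extension and the inside of the feet resting on the supports". Instruction: "Push the supports inwards without movement".
- **Hip Adduction.** Muscles: the adductor group. Position: seated, with "the outside of the knees resting on the supports". Instruction: "Push the supports out without movement".

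The article gives this table authority over how the exercises are done. Section 2.1.3 states: "The correct technical performance of the 8 specific exercises will be guided by the standards provided in Figure 1 and Table 3". Section 2.1.2 likewise sends the reader to Table 3 for positioning, muscles, contraction instructions and monitoring points.

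Section 2.2.1 lists seven secondary MVIC outcomes in Newtons. Hip abduction and hip adduction are two of them, and the mean and SD of change are given for each exercise separately.

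**The concern.** Abduction moves the limb away from the midline, so the force is outward and the outer side of the limb meets the support. Adduction is the reverse. Each hip row is therefore split: the name and muscle list describe one movement, while the contact side and push direction describe the opposite one.

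This matters because the two movements are separate reported outcomes. An operator who follows the instruction as written measures adductor force and files it as hip abduction, and the reverse for the other exercise. Section 2.2.1 justifies these outcomes by the training response in different body regions, and a swapped label would undo that purpose for the hip.

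A second possibility is that the rows are read in different ways. Section 2.1.2 has the trainer and the principal investigator lead the sessions; Section 2.2 has a physical activity professional and the study doctor carry out the assessments. If one reader follows the name and another the instruction, training targets set as a percentage of MVIC could come from the opposing muscles. If the reading changed between week 0 and week 17, a change score could mix two muscle groups. The article does not say that either will happen, but a contradictory standard leaves both open.

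**Working it through.** The article gives no figure to reproduce on this point. The check is a comparison within Table 3, followed by a count.

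**Step 1. Name, muscle and push direction, row by row**

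| Exercise | Main muscles listed | Push direction | Consistent? |
|---|---|---|---|
| Peck deck | Pectorals, anterior deltoid | To the body's centre | Yes |
| Pull over | Broad dorsal | Down | Yes |
| Lateral shoulder elevation | Middle deltoid | Up | Yes |
| Leg extension | Quadriceps | Forward | Yes |
| Leg curl | Hamstrings | Back | Yes |
| Low back | Square lumbar | Backwards | Yes |
| Hip abduction | Gluteals | Inwards | **No** |
| Hip adduction | Adductors | Out | **No** |

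Consistent: 6 of 8. Contradictory: 2 of 8 = 25%.

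**Step 2. Is it a single mistyped word?** No. In each hip row the contact side and the push direction agree with each other: inner side with inwards, outer side with out. Both disagree with the name and the muscles. Two cells in each of two rows make four reversed cells. Each reads as a complete statement in its proper column, so a broken table does not explain it.

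**Step 3. Is it corrected elsewhere?** Sections 2.1.2 and 2.2.1 and the Figure 1 caption use the two exercise names but give no push direction or contact side. Figure 1 panels g and h carry the same names, but the images are not available here.

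**Step 4. Outcomes exposed**

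- Secondary MVIC outcomes in Section 2.2.1: peck deck, pull over, lateral shoulder elevation, leg curl, low back, hip abduction, hip adduction = 7.
- Exposed to a label swap: 2/7 = 28.6%, about 29%.
- Primary outcomes (knee extensor MVIC, ASMMI) exposed: 0 of 2.

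**Step 5. A minor related point.** Both hip rows give 45° of hip extension for a participant seated against a backrest. The other seated lower-body and trunk rows state hip flexion: 90° for leg extension, 90° for leg curl and 60° for low back. The conclusion does not depend on this.

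**The case against.** The case for treating this as a small slip has real force.

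- **Figure 1 is a joint standard with Table 3 and cannot be seen.** If panels g and h are right, only the table text is wrong. This stands. The contradiction in the text is certain; the label swap is conditional.
- **Staff are qualified and supervise directly.** Section 2.1.3 requires a degree in sports science or physiotherapy and experience with older adults. Such a trainer, told to work the gluteals in hip abduction, would probably question an inward push. This lowers the risk but does not remove it, since the same section makes the table part of the guide to correct technique.
- **Even a consistent swap does limited harm.** Both muscle groups are trained, each percentage target comes from its own matching maximum, and each pre-post change remains a valid within-person contrast under the wrong name. The labels could be exchanged afterwards. This stands for a consistent swap, but not if readings differ between operators or visits.
- **The 29% counts only the MVIC secondary outcomes.** Grip strength, gait speed, quality of life and others are also secondary, and H1 to H3 do not use hip MVIC. This is correct, so the figure should be quoted only with its denominator.
- **Exchanging contact side and direction may not be the whole repair.** The rows also differ in set-up: foot contact with the knee straight, against knee contact with the knee at 100° of flexion. This is a fair point about the remedy, and the reason a check against Figure 1 is needed.

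**Conclusion.** The concern holds. Two of the eight rows in Table 3 contradict themselves, and no visible text resolves them. If the written instructions are followed, 2 of 7 secondary MVIC outcomes (29%) are reported under the opposing muscle group.

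That consequence assumes that operators follow the contact side and push direction and not the exercise name, and that Figure 1 does not lead them to the correct movement. Neither can be settled from the article. If the swap is consistent, training dose is unaffected. Both primary outcomes and the sample size are unaffected in any case. The correction should be made because the table is a working standard and is also what others would use to repeat the programme.

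**What to change.** Before the first week-0 test:

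1. Make name, muscles, contact side and push direction agree in both rows. Abduction: outer side of the limb on the support, push out. Adduction: inner side of the limb on the support, push in.
2. Check each complete set-up, including foot or knee contact and knee angle, against Figure 1 panels g and h. MVIC is recorded as force in Newtons, so moving the contact point changes the lever arm and hence the recorded value. Exchanging the exercise names would therefore define a different test from exchanging contact side and direction, and the sponsor must state which is meant.
3. Correct the hip extension angle given for a seated participant.
4. Use the same labels in the MVIC data fields.

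The cost is a text correction to two table rows and a check of two data labels. Design, sample size and analysis do not change.
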